**Methods/Design:**

The study participants will be 115 youth ages 8-15 y (45 with the syndrome and 70 without the syndrome but categorized as obese). The study will use a parallel design with the control group receiving the intervention after serving as control. Participants will be expected to complete a physical activity curriculum 4 days a week for 6 months including playground games 2 days a week and interactive console games 2 days a week. Parents will be trained at baseline and then provided with a curriculum and equipment to guide their implementation of the program. Tips related to scheduling and coping with barriers to daily program implementation will be provided. Throughout, parents will be contacted by phone once a week (weeks 1-4) and then every other week to receive support in between visits. Measurements of children and parents will be obtained at baseline, 12 weeks, and at the end (week 24) of the intervention. Children main outcomes include physical activity (accelerometry), body composition (dual x-ray absorptiometry), motor proficiency (Bruininks-Oseretsky Test of Motor Proficiency), quality of life and physical activity self-efficacy (questionnaires). Intervention compliance will be monitored using mail-in daily self-report checklists.

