## Methods/Design

### Study design

The Active Play @ Home study will evaluate the effectiveness of a 24-week PA intervention on select motor and health–related parameters in children with PWS and children with obesity but without PWS. The study has a quasi-experimental design with semi-random assignment to an intervention group or a wait-listed control group. The intervention group will consist of families with a child with PWS (n=35) and families with a child who is obese (n=50). Ten additional families with a child with PWS will be assigned to a wait-list control group and 20 families with an obese child without PWS will also serve as a wait-list group. Both wait-listed groups will serve as control groups prior to being enrolled in the PA intervention. Groups of two to four families will complete all baseline and follow-up testing on the same day throughout the study. The semi-random assignment consists of a priori established participant cohorts for both intervention and control groups. Upon recruitment, participants will be provided with tentative dates for their visits and their randomization to the cohort (intervention vs. control) will be based on their date preferences. Ethic committee approvals have been obtained from the California State University Fullerton Institutional Review Board and the United States Army Human Research Protection Office. During the first visit, after all study procedures are verbally explained, participants will have time to read the informed assent and consent forms and ask questions regarding the procedures. Afterwards, children participants will sign the informed assent form and their parents or guardians will sign the informed consent form. Figure 1 presents a timeline of the study procedures.

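### Arm is decided by the family's choice of visit date, not by chance, though the plan calls it randomization; season can then differ between arms and bias the group-by-time effect

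*Protocol article*

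**What the plan says.** All of this is in the protocol article, mainly under Study design.

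- Design label: "The study has a quasi-experimental design with semi-random assignment to an intervention group or a wait-listed control group". The abstract adds: "The study will use a parallel design with the control group receiving the intervention after serving as control".
- How cohorts are formed: "The semi-random assignment consists of a priori established participant cohorts for both intervention and control groups".
- How a family reaches a cohort: "Upon recruitment, participants will be provided with tentative dates for their visits", and then "their randomization to the cohort (intervention vs. control) will be based on their date preferences".
- Order of events: dates are offered at recruitment; consent and assent are signed at the first visit.
- Clustering by date: "Groups of two to four families will complete all baseline and follow-up testing on the same day throughout the study".
- Arm sizes: 35 PWS and 50 obese families in the intervention group, 10 PWS and 20 obese families in the wait-list group, so 85 against 30.

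Under Data analyses, the primary outcome (physical activity) is tested with a time by group by youth mixed ANOVA. Potential confounders may enter as covariates where appropriate; none is named. Under Physical activity, the outcome is accelerometry over one eight-day window per measurement, and families attend data collection on Saturdays.

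**The concern.** Randomization needs a chance step that neither the family nor the recruiter can influence. The mechanism described has none: each cohort already belongs to an arm, and the family's preferred date puts it in a cohort. Two consequences follow.

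**Selection.** Families able to attend on one set of dates may differ from those who prefer another set in work pattern, holidays, time pressure or motivation. In a parent-led programme on four days a week, those characteristics plausibly affect both adherence and the child's activity. In the formative interviews parents raised time burden and asked for a flexible schedule, so availability is not a neutral sorting variable. A recruiter who knows the link could also steer a family by the dates offered.

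**Calendar time.** Free-living activity can vary with season and school term, and some prescribed games can be played outdoors. Baseline and week 24 fall at different times of year, so each cohort's change includes a calendar component that depends on its start date. If start dates are distributed differently in the two arms, that component differs between arms and enters the group-by-time interaction. Taking pre-post differences does not remove it, because the bias lies in the change itself.

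At stake is whether a positive group-by-time result can be attributed to the intervention.

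**Working it through.** **1. Assignment mechanism.** Set the statements from Study design in order: cohorts are tied to an arm beforehand; the family is offered dates at recruitment; its preference selects the cohort; consent follows at the first visit. The arm is therefore a function of the chosen date and is settled before consent and baseline testing. The sequence contains no random element.

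**2. Number of date groups.** With 2 to 4 families per test date:
- control: 30/4 = 7.5 to 30/2 = 15, so about 8 to 15 date groups;
- intervention: 85/4 = 21.25 to 85/2 = 42.5, so about 22 to 42;
- PWS controls: 10/4 = 2.5 to 10/2 = 5, so about 3 to 5, if PWS and obese families never share a test day (the article does not say).

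With so few control date groups, calendar balance should be arranged by design and not left to chance.

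**3. The plan's own figure, to fix the scale.** Inputs from Data analyses: f = 0.20, alpha = 0.05, correlation 0.50, N = 84, power 0.95. For the within-between interaction with two groups and m = 2 time points, lambda = f² × N × m/(1 − rho) = 0.04 × 84 × 2/0.5 = 13.44 on 1 and 82 df. Power is 0.952, so 84 reproduces. With equal groups lambda = d² × N/4, so d = √(4 × 13.44/84) = √0.64 = 0.8 SD of change. That is the effect the study is sized to detect.

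**4. Illustration of calendar bias.** Assumptions: no true effect; the arms' calendar-driven change differs by s SD of change; dropout of 30% applies equally, leaving 85 × 0.7 = 59.5 and 30 × 0.7 = 21. The formula is lambda = s²/(1/59.5 + 1/21) = 15.52 × s², referred to a noncentral F with 1 and 78.5 df at the 5% critical value. For the full 85 against 30, the multiplier is 1/(1/85 + 1/30) = 22.17 and the df are 1 and 113.

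| Assumed s | lambda (59.5 vs 21) | Rejection, 59.5 vs 21 | Rejection, 85 vs 30 |
|---|---|---|---|
| 0.1 | 0.155 | 6.8% | 7.5% |
| 0.2 | 0.621 | 12.2% | 15.4% |
| 0.3 | 1.397 | 21.5% | 28.8% |
| 0.4 | 2.483 | 34.4% | 46.3% |

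The assumed biases are one eighth to one half of the planned 0.8 SD effect. The rates rise with sample size, so recruiting more families does not help. The calculation treats children as independent and ignores any correlation within a date cohort.

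**The case against.** The strongest reply is that the article largely discloses this: it calls the design quasi-experimental and the assignment semi-random, and it leaves room for confounders as covariates. That stands as disclosure. It does not remove selection by availability, and the same paragraph then uses the word randomization for a step that contains none.

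Four stronger readings are tempting, and the document does not support them.

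- *Season is confounded with arm.* No cohort dates are given and the timeline figure is not shown. Cohorts set in advance for both arms could be interleaved and balanced by design. Only the possibility is established.
- *Every cohort's change carries a near-maximal seasonal contrast.* A 24-week gap does not imply this. On a yearly cycle, a change over about half a year runs from its maximum to about zero depending on the start date.
- *Recruiters and families know the arm when dates are offered.* The article does not say so. What follows from the mechanism is that anyone who knows the link can foresee the arm. Concealment detail may sit in a fuller protocol.
- *The effect cannot be separated from season.* A calendar term could be added under the general covariate sentence; it is just not named.

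Saturday testing also weakens the idea that weekday school or ordinary weekday work sorts families. Holidays, weekend work and preference for a time of year remain. Finally, the 0.1 to 0.4 SD biases have no source in the document, so the error rates only illustrate.

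**Conclusion.** The allocation point is firm: assignment is by date preference within cohorts already tied to an arm, it is non-random and foreseeable from the date-to-arm link, and it is mislabelled. This rests on the article's own description and needs no assumption.

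The calendar point is a risk. Dates are nested within arm, no balancing of dates across arms is stated, and calendar time is not a named covariate, so seasonal change can differ between arms and bias the primary group-by-time comparison. Whether it does depends on cohort dates that are not shown. If the difference were 0.1 to 0.4 SD of change, the nominal 5% test would reject in about 7% to 34% of trials with no true effect (59.5 against 21 analysed, equal dropout, independent children). A bias from who chose which date would act in the same way and would not be removed by a season covariate. The matter should be put right before further slots are filled.

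**What to change.** **For slots not yet filled.** Keep the pre-set dates and let families choose among them. Have someone outside recruitment label the slots intervention or wait-list at random, in blocks of neighbouring dates, separately for PWS and obese families, in the planned ratios (35:10 and 50:20). Withhold the label from recruiters and families at least until the date is booked and consent is signed, and until baseline measurement is complete where the baseline training session allows. Families sharing a slot are then allocated together, so account for the date cohort in the analysis.

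**For slots already filled by preference.** Replace the word randomization with non-randomised assignment by date preference, and include the calendar period (month or school term) of each accelerometry week in the primary model. This addresses season; it does not correct for selection by availability, which should be stated as a limitation.

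**Cost.** A random list for dates that already exist, a rule on when the label is disclosed, and extra model terms; no additional participants. Families learn their arm later. The hands-on curriculum training takes place at baseline and the accelerometer is worn for eight days, so training may have to be scheduled after the label is disclosed, possibly at a separate contact. With few PWS control slots, the cohort adjustment will be imprecise in that stratum.

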**Figure 1 F1:**
[figure not shown]
Study timeline for the Active Play @ Home (APAH) intervention.

### Intervention description

This home-based intervention was developed by a team of experts with backgrounds in physical education, physical activity and obesity prevention in children, psychological aspects of physical activity, and motor control/learning. The intervention will consist of providing parents and children with a physical activity curriculum and its accompanying equipment needed to engage in four days of PA per week for 24 weeks. In addition, parents will be trained on the delivery of the Active Play @ Home curriculum, and will receive follow up support phone calls throughout the intervention.

Formative work done prior to designing the intervention includes the completion of group interviews with 28 parents of children and adults with PWS (2-22 years old) and a questionnaire completed by 90 parents with a child with PWS [16]. The group interviews indicated that most parents understood the benefits and the therapeutic role of PA for their children. The most frequently raised issues were as follows: the physical limitations associated with PWS may make it difficult to engage in PA; the children may consider PA to be more work than fun and therefore not enjoy it; the children may get easily frustrated, especially when the activities are too difficult to perform successfully; the parents may find the time spent in PA with their children too burdensome; and the cost of a PA program may be too expensive. Parents’ preferences for PA mode, frequency, and location for a successful PA program included: 1) Activities that can occur at home, in a caring, supportive, and non-competitive environment that foster participation from all family members; 2) interventions that include a variety of fun activities such as interactive console games, goal-oriented games, and dancing; 3) PA intervention materials such as a handbook or DVD with ideas for activities and hands-on instructions; and 4) a flexible schedule. The questionnaire findings emphasized the need to incorporate vigorous activities in the curriculum since children with PWS tend to spend more time engaging in moderate PA and much less time performing muscle and bone strengthening activities [16].

### Curriculum and parental support

The Active Play @ Home curriculum includes age-appropriate goal-oriented physical activities that combine playground and video games with specific exercises that target the following parameters: muscular strength and endurance, aerobic endurance, flexibility, balance, agility, and motor coordination. This curriculum was designed for children ages 8-11 years without disability and children ages 8-15 years with PWS. The curriculum includes playground games and interactive console-based games using the Nintendo Wii™, each of which are to be performed twice weekly. The duration of activity is systematically progressed from 25 to 45 minutes of MVPA over the course of the 24-week intervention. Both the parents and children will be trained to use the curriculum during a hands-on session at baseline. Each family receives the Active Play @ Home manual that contains a daily schedule detailing the activities for each of the four days of the week for the 24 weeks. The manual includes four sections: 1) introduction to the program that includes the philosophy guiding the program, a description of the motor skill and fitness components targeted, and a description of the parent’s role in leading the activities; 2) the daily schedule; 3) detailed descriptions of the playground games; and 4) instructions for playing the interactive console-based games. Each illustrated playground game is accompanied by instructions on how to carry out the activity, as well as instructional cues and modifications to assist the parent in leading the activities for his/her child (See Figure 2). In the interactive console-based games section of the manual we have included instructions on how to set-up the Nintendo Wii™ system and step-by step instructions for playing each of the selected games. Families receive all media equipment necessary as well as a variety of play balls, cones, hoops, foam mats, and boundary markers to be used throughout the intervention.

**Figure 2 F2:**
[figure not shown]
Sample playground game from the Active Play @ Home curriculum ([name], [name], [name], [name], and [name], 2011).

Over the 24-week program, parents will receive phone calls from a member of the research team who provides PA counseling and troubleshooting for parents regarding the implementation of the curriculum. Phone calls will take place every week during the first four weeks and then once every two weeks for the remainder of the intervention. In addition, the parents and children will complete physical activity checklists associated with each day of prescribed activity. The inclusion of self-monitoring techniques, along with discussions about planning and overcoming barriers into the parent training component of the program were considered to be important from the social cognitive theory perspective [24]. These regulatory skills of monitoring, planning/scheduling, and goal setting are incorporated into the baseline training of parents and during the follow-up phone calls [25]. The self-efficacy of children and parents will be targeted with the age-appropriate progressive nature of the curriculum that is designed to provide the opportunity for successful mastery experiences for the children. Further, self-efficacy in the children will be targeted through parents serving as skilled or learning models for the activity and providing verbal encouragement throughout the program.

### Measurements

Outcome measurements in children.

#### *Physical activity*

Physical activity will be measured using accelerometers, which provide detailed information on the temporal patterns (duration, frequency, and intensity) of PA. Data will be stored as acceleration counts recorded in 5-second epochs using the 4 MB GT3X (Actigraph, Pensacola, FL) triaxial activity monitor. This accelerometer model has excellent intra- and inter-instrument reliability across a wide range of accelerations and has been validated for use with children ages 10 to 15 years [53]. The accelerometer will be worn at the right hip and secured with an elastic belt. Children will wear the accelerometer for eight consecutive days (Sunday to Sunday) while awake. They will be instructed to remove the accelerometer for showering/bathing, swimming, or when going to bed. Initially the data will be screened for compliance of wear time (at least 10 hours per day on 3 weekdays and 1 weekend day). Non-wear periods will be defined as any period with 60+ consecutive minutes of missing data (0 counts). Because the families will participate in data collection on Saturdays, only accelerometry data collected on Sundays will be eligible for analyses for a weekend day. To determine thresholds for sedentary, light, moderate, and vigorous physical activity we will use the children cut-points established by Evenson et al. (2008) [54]. These cut-points were recently recommended as the best choice for categorizing physical activity intensities in children [55]. In addition, the parent with his/her child will also complete a log of all the physical activities the child engages in over the eight-day period.

#### *Motor proficiency*

Motor proficiency will be evaluated using the long form version 2 of the Bruininks-Oseretsky Test of Motor Proficiency (BOT-2) [56]. The BOT-2 is composed of 53 items and provides a total motor composite score across 4 domains: fine manual control (fine motor precision and fine motor integration), manual coordination (manual dexterity and upper limb coordination), body coordination (bilateral coordination and balance), and strength and agility (running speed and agility and strength). We expect to see baseline differences between the children and youth with PWS and those without PWS in all domains and composite areas. In addition, we expect significant improvements following completion of the PA intervention in the areas of upper limb coordination, bilateral coordination, balance, running speed, and agility and strength. As fine manual control and manual dexterity are not targeted in this intervention, change in these parameters will not be assessed. The BOT-2 is designed to identify individuals with mild-to-moderate coordination deficits and has been validated for use in 4–21 year olds [56]. A sub-sample of participants with PWS will complete the BOT-2 twice at baseline, separated by an interval of one week, to determine test-retest reliability.

#### *Sensory-motor reception and integration*

The evaluation of sensory reception and motor integration is an exploratory component of this study. The intent is to first establish the validity and reliability of the Sensory Organization Test® (SOT) when administered to children and adolescents with PWS on two days separated by a week in a small sub-sample of participants. The same sub-sample will also perform the SOT at regular interventions during the intervention period to determine if any changes in sensory reception and integration occur as a result of the intervention.

The SOT is designed to identify impairments in one or more of the three sensory systems (i.e., vision, somatosensory, vestibular) that contribute to standing balance. This test has been previously used with pediatric populations, with and without disabilities [57]. The test is comprised of six test conditions. *Condition one* serves as the control condition because there is no manipulation of the sensory environment. In *condition two*, vision is removed by having the participant wear a blindfold while standing on a stable support surface, whereas in *condition three*, vision is manipulated by sway-referencing the visual three-sided surround as the participant stands quietly on a stable support surface. In *condition four*, somatosensory inputs are manipulated by sway-referencing the support surface. Specifically, the support surface is rotated in an anterior or posterior (AP) direction in direct response to the sway generated by the standing participant. The ratio of support surface movement to AP sway of the participant is 1:1. In *condition five*, the support surface is once again sway-referenced but vision is also removed by having the participant wear a blindfold. Finally, in *condition six*, input from the visual and somatosensory systems are removed. For the SOT, all participants will be required to wear an overhead safety harness to ensure their safety during practice and test trials. Each participant will stand on the force platform of the Smart Balance Master® with the arms extended and to the sides of the body. The participants’ feet will be positioned in accordance with the manufacturer’s requirements for data collection (i.e., feet facing forward and the medial malleolus and the lateral calcaneus aligned with a grid superimposed on the surface of the force plate). The alignment of the feet is based on the individual’s height and done to ensure consistency of foot position across testing sessions.

During the first testing session, the test will be verbally explained to the participants after which they will physically perform one trial in each of the six sensory conditions. This practice trial is intended to familiarize them with the equipment, harness, and actual test protocol. Following a three-minute rest interval, participants will then perform three 20-second trials in each of the six sensory conditions. Participants will be permitted to rest as needed throughout the test.

